## Abstract

**Background::**

Nausea and vomiting are among the most common and distressing side effects of chemotherapy. Difference in views about the effectiveness of auricular acupuncture (AA) versus electroacupuncture (EA) of chemotherapy-induced nausea and vomiting (CINV) lies at the heart of the debate. The aim of this study is to compare the antiemetic efficacy and safety of AA and EA for CINV.

**Methods::**

One hundred twenty participants, 18 to 75 years old malignant tumors will receiving chemotherapy with cisplatin, will be recruited and randomized into 3 groups equally, Group A (the AA group), Group B (the EA group), and Group C (the control group). The participants in Group A and Group B will receive AA or EA regimens, alternatively, beginning on the day before first day of chemotherapy for a third consecutive cycles. All participants will continue to receive conventional treatment. The incidence and severity of CINV will be assessed using the definition and classification of nausea and vomiting (NCI-CTC AE4.0) and the MASCC (Multinational Association for Supportive Care in Cancer) Antiemesis Tool (MAT). Secondary outcome measures include the degree of abdominal distension, the first time of flatus and defecation, and life quality. Additionally, adverse events will also be documented during the period of the treatment.

**Discussion::**

This trial may provide evidence regarding the clinical effectiveness and safety of AA versus EA for CINV following cisplatin-based regimens.

**Trail registration::**

This study is registered with the Chinese Clinical Trial Registry: ChiCTR2000040942.

## Introduction

1

Chemotherapy-induced nausea and vomiting (CINV) is among the most common and distressing side effects of chemotherapy.^[1]^ It has been shown to significantly affect the quality of life (QoL) and daily function of patients receiving chemotherapy.^[2]^ Moreover, CINV, as a prognostic factor for overall survival, is so severe in some cases that it interrupts the treatment of primary cancer and increases the risk of disease progression,^[3,4]^ which result in treatment-outcome reduction.^[5]^

Cisplatin, which is a cornerstone of chemotherapy for the treatment of multiple cancers, is a highly emetogenic chemotherapy drug.^[6]^ Over 90% cancer patients will vomit within the first 24 hours after the administration of cisplatin-based chemotherapy unless antiemetic drugs are used.^[7]^ Even with the guideline-recommended antiemetic drugs, cisplatin-induced vomiting is controlled in only 60% of patients; therefore, considerable numbers of patients still experience nausea.^[8]^

Although the mechanisms underlying CINV are not clear enough,^[9]^ to date, commonly prescribed medicines,^[10]^ for nausea and vomiting are: 5-hydroxytryptamine-3 serotonin receptor antagonists (5-HT3RA), Neurokinin1 receptor antagonists (NK-1RA), and corticosteroid.^[11]^ However, for all its prominence in CINV management, these drugs are subject to considerably economic burden and side effects, namely insomnia, headaches, dizziness, and constipation.^[12]^ Thus, additional treatments are urgently needed to effectively manage and ameliorate chemotherapy-induced nausea and vomiting (CINV), without those defects in the wake of antiemetic drugs.

An increasing body of evidence points that electroacupuncture (EA) may provide modest benefits in the treatment of CINV.^[13]^ However, the spread of it is surprisingly slow, and EA is still judged as a highly suggestive but not conclusive treatment.^[14–17]^ For certain patients, they are reluctant to accept EA treatment for their intolerance to needling. The problems and limits of EA center on how it manipulate. Thus, auricular acupuncture (AA) might be a sound treatment to feather all patients’ needs for convenience and comfort. Compared with a pile of studies conducted the access to the effectiveness of EA against CINV, the role of AA has received less attention,^[18]^ and the literatures on AA are limited in number with uncertain quality.

To our knowledge, there are no randomized controlled trails comparing the effect and safety of AA versus EA in cancer patients who experience CINV. Therefore, the present study is designed to determine the efficacy and safety of AA versus EA in ameliorating CINV among patients receiving cisplatin-based regimens.

## Methods

2

### Study design

2.1

This is a singular center, randomized, placebo-controlled clinical trial. Using a balanced random approach, all participants will be recruited and assigned to 3 groups: Group A (the AA group), Group B (the EA group), and Group C (the control group), after meeting the eligibility criteria, and completing informed consent.

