### Intervention

2.4

Participants in all groups will receive conventional Western medical treatments as recommended by the Guidelines of Chinese Society of Clinical Oncology: Prevention and treatment of nausea and vomiting caused by antitumor therapies,^[21]^ including 5-HT3 receptor antagonist, NK-1 receptor antagonist, dexamethasone, and so on. In addition to conventional treatment, patients in Group A and Group B will receive AA or EA regimens, alternatively.

Patients receiving acupuncture therapy will be treated bilaterally at 2 distal acupoints: Neiguan (PC6) and Zusanli (ST36). PC6 is an acupoint of the pericardium meridian. It is located between the palmaris longus tendon and the flexor carpi radialis muscle tendon, 2 cun above the rasceta. ST36 is located on the anterolateral side of the lower leg, 3 cun below Dubi and one finger width lateral of the anterior border of the tibia. The location of these acupoints is described in The National Standard of Acupoint Location. Detailed information on the acupuncture treatment is provided in Table 1.

**Table 1 T1:** Detailed information about acupuncture treatment according to STRICTA guideline.

Item	Detail	Detail response
1. Acupuncture rationale	(1a) Style of acupuncture (e.g., Traditional Chinese Medicine, Japanese, Korean, Western medical, five element, ear acupuncture, etc)	Group A: Auricular acupuncture, also named as ear acupunctureGroup B: Electroacupuncture
	(1b) Reasoning for treatment provided, based on historical context, literature sources, and/or consensus methods, with references where appropriate	Selected acupoints based on literature review and clinical experience
	(1c) Extent to which treatment was varied	No variation
2. Details of needling	(2a) Number of needle insertions per subject per session (mean and range where relevant)	4
	(2b) Names (or location if no standard name) of points used (uni/bilateral)	Neiguan (PC6) and Zusanli (ST36)Bilaterally used
	(2c) Depth of insertion, based on a specified unit of measurement, or on a particular tissue level	Group A: 1.2 mmGroup B: 1–2 cm
	(2d) Response sought (e.g., *de qi* or muscle twitch response)	Group A: PainGroup B: *de qi*
	(2e) Needle stimulation (e.g., manual, electrical)	Group A: NoneGroup B: Electrical
	(2f) Needle retention time	Group A: 1 dayGroup B: 30 min

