	(2g) Needle type (diameter, length, and manufacturer or material)	Group A: Sterile intradermal acupuncture needles (PYONEX, 0.21.2 mm, SEIRIN Corporation, Japan)Group B: Sterile single-use needles (Shukang, ϕ0.25 × 40 mm, Changchun Aikang Medical Devices Co., Ltd., China)
3. Treatment regimen	(3a) Number of treatment sessions	Three consecutive chemotherapy cycles
	(3b) Frequency and duration of treatment sessions	Once a day
4. Other components of treatment	(4a) Details of other interventions administered to the acupuncture group (e.g., moxibustion, cupping, herbs, exercises, lifestyle advice)	None
	(4b) Setting and context of treatment, including instructions to practitioners, and information and explanations to patients	The same practitioner will treat every session for 1 participant.
5. Practitioner background	(5) Description of participating acupuncturists (qualification or professional affiliation, years in acupuncture practice, other relevant experience)	Licensed Traditional Chinese medicine doctor with >5 years of acupuncture treatment experience
6. Control or comparator interventions	(6a) Rationale for the control or comparator in the context of the research question, with sources that justify this choice	No acupuncture will be performed on the control group
	(6b) Precise description of the control or comparator. If sham acupuncture or any other type of acupuncture-like control is used, provide details as for Items 1 to 3 above.	No sham acupuncture will be performed on the control group

Participants in Group A will receive the following treatment. After each insertion site be disinfected with 75% alcohol, sterile intradermal acupuncture needles (PYONEX, ϕ0.2 × 1.2 mm, SEIRIN Corporation, Japan) will be inserted vertically to a depth of 1.2 mm. Participants will be requested to put pressure on the each auricular point for about 15 seconds per one time, 3 times per day.

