As for the participants in Group B, Shukang brand needles (size 0.25 mm × 40 mm) made by Changchun Aikang Medical Devices Co., Ltd., China, will be used to perform the acupuncture treatments. Stimulation will be applied until the patient experiences de qi (obtains qi). A patient's experience of de qi may take on multiple unique manifestations at the needle site itself and/or around the site of needle manipulation including soreness, aching, numbness, tingling, and even warmth. Electrical stimulation of acupuncture needles will be done at the frequency of 15 Hz with continuous wave in order to ensure patient comfort, lasting 30 minutes.

Participants in the above 2 groups will individually be needled for 4 days, beginning on the day before first day of chemotherapy and ending on the last day of it. The intervention will be applied for a third consecutive cycle. Only well-trained acupuncturists with >5 years of clinical experience could conduct acupuncture manipulation.

Subjects in the control group (Group C) will not receive acupuncture treatments. They will receive conventional Western medicine treatment only.

All patients undergo supervision and evaluation of curative effect at 10 am daily, until discharge. A third party will perform all data analysis. The flow chart of this trial is shown in Fig. 1.

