### Randomization and blinding

2.7

Randomization of subjects to 2 groups will be on the basis of a concealed allocation approach using statistical analysis PROCPLAN statements (SAS 9.4; World Headquarters SAS Institute Inc., Cary, NC). A computer-generated list of random numbers will be used to determine the allocation of the participants, with numbered opaque sealed envelopes containing the randomization schedule. The envelopes will be kept by an investigator who is not an assessor in the study and will be informed of the outcomes at the end of the study. In this trial, participants and acupuncture practitioners cannot be blinded. The researchers recording the outcomes and those making the conclusions will be all blinded to patients’ assessments.

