## Discussion

3

Acupoint therapies, including EA and AA, have the characteristics of higher acceptability, limit side effects, and inexpensiveness.^[22]^ And yet, the fast growing piles of studies, especially low to moderate evidences,^[23,24]^ do not give us any firm grasp of reasoned acupuncture regimen for preventing CINV. The shortage of the studies which compare different acupuncture therapies cause that clinicians are unable to determine the therapeutic values of them, which is unavailable for selecting the most appropriate treatment.^[25]^ Rather, this is not the whole story. To our best knowledge, there is no single regimen could completely blocking CINV.^[26]^ Therefore, relative studies should focus on all categories of CINV. Unfortunately, most previous researches paid more attention on acute CINV, while delayed CINV is a more common, severe and hard-to-cure subtype.^[27]^ To meet the clinic needs, we design this trail to compare the effectiveness and safety of EA and AA for CINV induced by cisplatin-based regimens in a strictly devised situation, and develop a standardized alternative therapy for medical staff.

To minimize the bias, stratified block randomization and blinding will be applied, and participants will be avoided any communication with others farthest, shaped by separate treatment time and diagnosis rooms.

Despite its strengths, this study has, nevertheless, an obvious limitation. It is a single-center study, which may limit its generalizability so a future multiple-center large-sample size study will be needed. However, the results of this trail will provide more evidence and will help medical staffs make a better choice for patients.

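### The trial is labelled placebo-controlled, but Group C gets no placebo or sham and patients know their group, so comparisons with Group C are not placebo-adjusted

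*Protocol article*

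**What the plan says.** **Label.** Section 2.1 (Study design) reads: "This is a singular center, randomized, placebo-controlled clinical trial".

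**Control arm.** Table 1, item 6a: "No acupuncture will be performed on the control group". Item 6b: "No sham acupuncture will be performed on the control group". Section 2.4 says of Group C: "They will receive conventional Western medicine treatment only". The antiemetic background is common to all three arms: "Participants in all groups will receive conventional Western medical treatments as recommended by the Guidelines of Chinese Society of Clinical Oncology".

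**Blinding.** Section 2.7 states: "In this trial, participants and acupuncture practitioners cannot be blinded". It adds that the researchers who record outcomes and "those making the conclusions will be all blinded to" patients' assessments. Section 2.8 plans blinded estimation and statistics by a third person. The Discussion says, as a means of reducing bias, that "stratified block randomization and blinding will be applied". The one limitation it names is the single centre.

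**Outcomes.** The primary outcome (Section 2.5.1) is the NCI-CTC AE grading of nausea and vomiting together with the MAT, whose items cover whether nausea and vomiting occurred, how often the patient vomited and how strong the nausea was. Secondary outcomes (Section 2.5.2) include a distension score and quality of life.

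**The concern.** A placebo-controlled label tells the reader that patients in the control arm had something resembling the active treatment, so that a difference from control can be read as net of expectation. Nothing of that kind is described for Group C.

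This matters because several outcomes are symptoms that only the patient can report. Groups A and B are needled for 4 days per cycle, and Group A patients also press the points three times a day. Group C has no matching contact. A difference from Group C would combine any effect of the needles with expectation, extra attention and the way unblinded patients report. If the label is carried into the results paper, A versus C and B versus C could be read as placebo-adjusted when they are not.

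**Working it through.** No figure in the plan turns on this point, so there is none to reproduce. The check is to set the statements side by side.

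| Question | What the protocol article states | Where |
|---|---|---|
| Is there a placebo? | The label says yes | Section 2.1 |
| Does Group C get needling? | No | Table 1, item 6a |
| Does Group C get sham? | No | Table 1, item 6b |
| What does Group C get? | Conventional treatment only | Section 2.4 |
| Do A and B get the same background treatment? | Yes | Section 2.4 |
| Are patients and practitioners blinded? | No | Section 2.7 |
| Are recorders and analysts blinded? | Yes, though the wording in 2.7 says to assessments, not to allocation | Sections 2.7, 2.8 |

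1. The background treatment is the same in all arms and Group C receives nothing further. The contrast with Group C is add-on versus no add-on.
2. No placebo drug, device or procedure appears anywhere in the article. The label in Section 2.1 cannot be reconciled with Table 1 and Section 2.4.
3. The level of nausea, the distension score and quality of life originate with the patient. The article does not say that the MAT is self-completed. That its content comes from the patient follows from its items. A blinded recorder or analyst cannot remove a bias that is already in the patient's answer.
4. A versus C and B versus C therefore estimate the whole package. A versus B does not involve the placebo label, although it too is open-label and the two procedures differ.

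**Illustration, on assumed values only.** Take n = 40 per arm (Section 2.6) and a two-sided 0.05 test (Section 2.8). Assume a true event rate of 40% in both arms, hence no needle effect, and suppose that unblinded patients in an acupuncture arm under-report by b.

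- Reported rates: p_C = 0.40 and p_A = 0.40 − b, with pooled p̄ = 0.40 − b/2.
- SE0 = √[2p̄(1 − p̄)/n] and SE1 = √[p_C(1 − p_C)/n + p_A(1 − p_A)/n].
- Chance of significance = Φ[(b − 1.96·SE0)/SE1] + Φ[(−b − 1.96·SE0)/SE1].

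For b = 0.10:

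- SE0 = √(2 × 0.35 × 0.65/40) = 0.1067.
- SE1 = √(0.24/40 + 0.21/40) = 0.1061.
- The two terms are about 0.152 and 0.002, which gives 0.154.

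| Assumed under-reporting b (points) | Chance of a significant difference from Group C |
|---|---|
| 0 | 5% |
| 5 | 7% |
| 10 | 15% |
| 15 | 30% |
| 20 | 50% |

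The table shows how sensitive the comparison would be. It does not estimate the bias in this trial.

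**The case against.** The case on the other side is that this is a label error in an otherwise open account. Much of that stands. Section 2.7 says plainly that patients and practitioners are not blinded, Table 1 says plainly that there is no sham, and an add-on design with a usual-care control is legitimate. Four stronger readings are tempting, and the documents do not support them.

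- *The trial presents itself as blinded when it has no blinding.* Section 2.1 does not use the word. Blinded recorders and analysts are planned in Sections 2.7 and 2.8. Only the Discussion speaks of blinding without qualification. The odd object of blinding in 2.7 may be a slip for assignments. It needs correcting, but it does not show that allocation is known to the recorders.
- *The trial claims a specific needle effect.* No such conclusion is written. The aim in the Abstract, Introduction and Discussion is auricular acupuncture versus electroacupuncture. The problem lies in what the label invites a reader to conclude about Group C.
- *Assessors will see the Group A needles.* Table 1 gives one-day retention and Section 2.4 a daily evaluation at 10 am, but no times of insertion or removal are given. Whether needles are in place at the primary time points is therefore an inference.
- *Counted vomiting episodes should become the primary measure.* Vomiting occurrence and frequency are already part of the primary outcome. MAT counts would still come from the same unblinded patients, and a new endpoint would be far more than a wording change.

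What the objection does not remove is the contradiction itself: Section 2.1 asserts a property that Table 1 and Section 2.4 rule out.

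**Conclusion.** The point holds: wrong as written. Section 2.1 states a design property that the trial does not have. The consequence is confined to the two comparisons with Group C and bears chiefly on outcomes that rest on the patient's report. For these, the estimate is of acupuncture added to standard care, with expectation, attention and reporting effects included.

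The size of those effects cannot be taken from the documents. The 5% to 50% range rests on an assumed 40% event rate and assumed under-reporting of 0 to 20 points. It would be circular to go further, assume that some given difference is all expectation, and then conclude that no effect remains. The conclusion about the label needs none of these assumptions. It does rest on the inference that MAT nausea items, distension and quality of life come from the patient.

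**What to change.** - **Section 2.1:** replace the placebo-controlled label with *open-label, usual-care-controlled, with blinded outcome recorders and analysts*.
- **Section 2.7:** replace the reference to patients' assessments with *blinded to group allocation*, once the sponsor confirms that this is what is meant, and state that patient-reported outcomes are not blinded.
- **Discussion:** qualify the mention of blinding in the same terms, and add unblinded patient-reported outcomes to the limitations.
- **Conclusions against Group C:** limit them to *acupuncture plus standard care versus standard care alone*.

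Leave the primary endpoint, the sample size and the comparison of the two acupuncture arms as they are. The cost is a few sentences and a more modest claim against control. No new procedure or data is needed.

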### Ethics

2.2

This trial will be accomplished strictly followed the principles for medical ethics outlined in the 2013 updated Declaration of Helsinki. The study was approved by the Ethics and Research Committee of Chengdu Second People's Hospital, China (ethics reference: 2020077). This committee is an ethical approval committee organized by leading professors in their own fields. It will be obtained from all participants in advance that written and signed informed consent. This trial has been registered on www.chictr.org.cn/edit.aspx?pid=63281&htm=4 (ChiCTR2000040942) at December 16, 2020 and will be reported squared with the CONSORT statement,^[19]^ as well as STRICTA (Standards for Reporting Interventions in Clinical Trials of Acupuncture).^[20]^ The Chinese Cochrane Center is responsible for the whole trial including the randomization, blinding, statistical analyses, data management, and monitoring.

### Population

2.3

All participants will be recruited from the Oncology Department of Chengdu Second People's Hospital, a tertiary hospital, which plays the leading role at the local. We will recruit cases diagnosed with magnificent tumor confirmed by clinicopathology or cytology undergoing the cisplatin-based chemotherapy regimens. Participants who fulfil the inclusion criteria and sign informed consent forms will enter the screening period, otherwise will be excluded before randomization. Chengdu is the largest base of industrial technology and commercial and financial center in the west of China, with a population of 14,047,600, where could collect more cases of diversity. The duration of enrollment is from December 31, 2020 to December 30, 2022.

Eligible participants are all adults aged 18 to 75 years, diagnosed with magnificent tumor confirmed by clinicopathology or cytology undergoing the cisplatin-based chemotherapy regimens and an expected survival time of >3 months. They are still in relatively good physical condition, with a Kamofsky score >60.

The exclusion criteria are as follows: nausea and vomiting caused by intracranial or other metastases, severe gastrointestinal obstruction, or combine organic disorders; recent using drugs may cause nausea and vomiting; participants with allergy history, especially to metal and tape; participants with inability to communicate; participants participating in another clinical trial within 3 months.

The withdrawal criteria are as follows: terminate or adjust the chemotherapy regimen after evaluation by oncologists due to clinical exacerbation; at the patient's own request or at the request of their legal representative.

### Intervention

2.4

Participants in all groups will receive conventional Western medical treatments as recommended by the Guidelines of Chinese Society of Clinical Oncology: Prevention and treatment of nausea and vomiting caused by antitumor therapies,^[21]^ including 5-HT3 receptor antagonist, NK-1 receptor antagonist, dexamethasone, and so on. In addition to conventional treatment, patients in Group A and Group B will receive AA or EA regimens, alternatively.

Patients receiving acupuncture therapy will be treated bilaterally at 2 distal acupoints: Neiguan (PC6) and Zusanli (ST36). PC6 is an acupoint of the pericardium meridian. It is located between the palmaris longus tendon and the flexor carpi radialis muscle tendon, 2 cun above the rasceta. ST36 is located on the anterolateral side of the lower leg, 3 cun below Dubi and one finger width lateral of the anterior border of the tibia. The location of these acupoints is described in The National Standard of Acupoint Location. Detailed information on the acupuncture treatment is provided in Table 1.

**Table 1 T1:** Detailed information about acupuncture treatment according to STRICTA guideline.

Item	Detail	Detail response
1. Acupuncture rationale	(1a) Style of acupuncture (e.g., Traditional Chinese Medicine, Japanese, Korean, Western medical, five element, ear acupuncture, etc)	Group A: Auricular acupuncture, also named as ear acupunctureGroup B: Electroacupuncture
	(1b) Reasoning for treatment provided, based on historical context, literature sources, and/or consensus methods, with references where appropriate	Selected acupoints based on literature review and clinical experience
	(1c) Extent to which treatment was varied	No variation
2. Details of needling	(2a) Number of needle insertions per subject per session (mean and range where relevant)	4
	(2b) Names (or location if no standard name) of points used (uni/bilateral)	Neiguan (PC6) and Zusanli (ST36)Bilaterally used
	(2c) Depth of insertion, based on a specified unit of measurement, or on a particular tissue level	Group A: 1.2 mmGroup B: 1–2 cm
	(2d) Response sought (e.g., *de qi* or muscle twitch response)	Group A: PainGroup B: *de qi*
	(2e) Needle stimulation (e.g., manual, electrical)	Group A: NoneGroup B: Electrical
	(2f) Needle retention time	Group A: 1 dayGroup B: 30 min
	(2g) Needle type (diameter, length, and manufacturer or material)	Group A: Sterile intradermal acupuncture needles (PYONEX, 0.21.2 mm, SEIRIN Corporation, Japan)Group B: Sterile single-use needles (Shukang, ϕ0.25 × 40 mm, Changchun Aikang Medical Devices Co., Ltd., China)
3. Treatment regimen	(3a) Number of treatment sessions	Three consecutive chemotherapy cycles
	(3b) Frequency and duration of treatment sessions	Once a day
4. Other components of treatment	(4a) Details of other interventions administered to the acupuncture group (e.g., moxibustion, cupping, herbs, exercises, lifestyle advice)	None
	(4b) Setting and context of treatment, including instructions to practitioners, and information and explanations to patients	The same practitioner will treat every session for 1 participant.
5. Practitioner background	(5) Description of participating acupuncturists (qualification or professional affiliation, years in acupuncture practice, other relevant experience)	Licensed Traditional Chinese medicine doctor with >5 years of acupuncture treatment experience
6. Control or comparator interventions	(6a) Rationale for the control or comparator in the context of the research question, with sources that justify this choice	No acupuncture will be performed on the control group
	(6b) Precise description of the control or comparator. If sham acupuncture or any other type of acupuncture-like control is used, provide details as for Items 1 to 3 above.	No sham acupuncture will be performed on the control group

Participants in Group A will receive the following treatment. After each insertion site be disinfected with 75% alcohol, sterile intradermal acupuncture needles (PYONEX, ϕ0.2 × 1.2 mm, SEIRIN Corporation, Japan) will be inserted vertically to a depth of 1.2 mm. Participants will be requested to put pressure on the each auricular point for about 15 seconds per one time, 3 times per day.

As for the participants in Group B, Shukang brand needles (size 0.25 mm × 40 mm) made by Changchun Aikang Medical Devices Co., Ltd., China, will be used to perform the acupuncture treatments. Stimulation will be applied until the patient experiences de qi (obtains qi). A patient's experience of de qi may take on multiple unique manifestations at the needle site itself and/or around the site of needle manipulation including soreness, aching, numbness, tingling, and even warmth. Electrical stimulation of acupuncture needles will be done at the frequency of 15 Hz with continuous wave in order to ensure patient comfort, lasting 30 minutes.

Participants in the above 2 groups will individually be needled for 4 days, beginning on the day before first day of chemotherapy and ending on the last day of it. The intervention will be applied for a third consecutive cycle. Only well-trained acupuncturists with >5 years of clinical experience could conduct acupuncture manipulation.

Subjects in the control group (Group C) will not receive acupuncture treatments. They will receive conventional Western medicine treatment only.

All patients undergo supervision and evaluation of curative effect at 10 am daily, until discharge. A third party will perform all data analysis. The flow chart of this trial is shown in Fig. 1.

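### The protocol article contradicts itself on where Group A is needled: wrist and leg points for all acupuncture patients, yet an ear acupuncture arm for which no ear point is named

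*Protocol article*

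**What the plan says.** The stated aim in the Abstract and Introduction of the protocol article is to compare auricular acupuncture (Group A) with electroacupuncture (Group B). Group C receives conventional treatment only.

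On the site of needling, the article says the following.

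- **Section 2.4, general sentence:** "Patients receiving acupuncture therapy will be treated bilaterally at 2 distal acupoints: Neiguan (PC6) and Zusanli (ST36"). The sentence is not limited to Group B, and the same section later says that both Group A and Group B are needled.
- **Section 2.4, locations:** of PC6, "It is located between the palmaris longus tendon and the flexor carpi radialis muscle tendon, 2 cun above the rasceta"; and "ST36 is located on the anterolateral side of the lower leg".
- **Table 1, item 1a:** Group A is auricular (ear) acupuncture and Group B is electroacupuncture.
- **Table 1, item 2a:** a single entry of 4 insertions per session, with no group split.
- **Table 1, item 2b:** a single entry, "Neiguan (PC6) and Zusanli (ST36)Bilaterally used", with no group split.
- **Section 2.4, Group A paragraph:** "Participants will be requested to put pressure on the each auricular point for about 15 seconds per one time, 3 times per day".
- **Table 1, item 2e (needle stimulation):** "Group A: NoneGroup B: Electrical".

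**The concern.** The site of stimulation is what makes an intervention auricular. On that feature the article gives two incompatible accounts of Group A. One puts the needles at a wrist point and a lower-leg point. The other puts them in the ear but never says where.

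What is at stake is the contrast being estimated. If the two arms share PC6 and ST36, A versus B compares retained intradermal needles with electrical stimulation at the same body points, and A versus C tests intradermal needling at body points against no acupuncture. Neither would inform on auricular acupuncture. If ear points are meant, the printed description of Group A is wrong on site, and a reader could not reproduce the arm from it. No later analysis can recover the intended contrast if the arm was delivered in a way that does not match the claim.

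**Working it through.** No sample size or power figure bears on this point, so the check is mainly a comparison of passages.

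**Step 1. Do the PC6/ST36 statements reach Group A?** The general sentence in Section 2.4 covers patients receiving acupuncture, and Section 2.4 has both A and B needled. As printed, it includes Group A.

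**Step 2. Does Table 1 limit them to Group B?** Table 1 separates the groups where it means to. Item 1a and items 2c to 2g each carry a Group A and a Group B entry; depth, for example, reads "Group A: 1.2 mmGroup B: 1–2 cm". Items 2a and 2b, which lie between these split rows, have one entry each. As printed, they apply to both arms.

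**Step 3. Could PC6 or ST36 be on the ear?** No. By the article's own description, PC6 lies above the wrist and ST36 on the lower leg.

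**Step 4. Is an ear point given elsewhere?** The Group A paragraph tells patients to press each auricular point, but the text shown does not name, locate or count any.

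**Step 5. Does the insertion count decide the matter?** Item 2a gives 4. The named points reproduce it: 2 points × 2 sides = 4. So would any other two points used on both sides, including two ear points on both ears (2 × 2 = 4), or four ear points on one side (4 × 1 = 4). The count agrees with item 2b but does not distinguish the readings.

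**Step 6. What follows under each reading?**

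| Reading | Group A receives | Consequence |
|---|---|---|
| Items 2a and 2b apply to both arms, as printed | Intradermal needles at PC6 and ST36 | A versus B differs in needle type, depth, retention and stimulation, not in ear versus body; no conclusion on auricular acupuncture |
| PC6 and ST36 were meant for Group B only | Ear points, not named | The Section 2.4 sentence and item 2b are wrong for Group A; its points and their number are unstated |

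The text needs correction under either reading.

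**Step 7. How much of the trial is touched?** Section 2.6 plans 40 patients per group, 120 in all: 40/120 = one third. Three arms give three pairwise comparisons (A–B, A–C, B–C), of which two involve Group A.

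**The case against.** The strongest reply is that ear points were plainly intended. The aim, the group names, the rationale in the Introduction (an option for patients who do not tolerate needling), item 1a and the pressing instruction all point that way. Against them stand one general sentence and one unsplit table cell, which may simply be Group B's points written without a group label. An article also condenses, and a list of ear points may exist in a fuller protocol. The treating acupuncturists are trained and have more than five years' experience, so they may not work from this text at all.

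Much of this stands. The absence of an ear-point list would not by itself be a finding, and confusion among practitioners is a possibility rather than something the article shows. What the reply does not remove is item 2b. Table 1 is offered as the detailed treatment description to the STRICTA standard, and it states a location that conflicts with item 1a and the Group A paragraph. A fuller document could explain that conflict but would not make the printed entries agree.

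Some stronger readings are tempting, and the documents do not support them.

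- **That Group A is in fact needled at body points, by design.** Nothing shows that the sponsor chose this. It is an inconsistency, and the intended sites are not determinable from the text.
- **That 4 insertions can only mean PC6 and ST36.** Step 5 shows otherwise.
- **That the entry of no variation in item 1c means the arms share points.** It cannot mean that the arms are alike, because the same table gives them different styles, depths, retention times and needles. It more naturally says that treatment is not individualised between patients.
- **That item 2e flatly contradicts the pressing instruction.** The entry for Group A may mean that the practitioner applies no stimulation, while patients press the points themselves. It deserves clarification but is secondary.

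**Conclusion.** The point holds as an internal inconsistency in the description of one randomised intervention. Section 2.4 and Table 1 item 2b put Group A's needles at PC6 and ST36; item 1a and the Group A paragraph put them in the ear. Followed as printed in item 2b, the trial would not answer its auricular versus electroacupuncture question. If ear points are used, the printed specification is wrong for Group A.

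The contradiction covers all 40 planned Group A patients, one third of the trial, and two of three pairwise comparisons. It should be resolved because the identity of an experimental arm depends on it. The conclusion assumes only that the unsplit entries in Table 1 mean what they say. It does not assume which sites were intended, and it does not rest on the insertion count or on item 1c.

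**What to change.** - Reconcile the general sentence in Section 2.4, Table 1 items 1a, 2a and 2b, and the Group A paragraph. State the points and the number of insertions separately for Group A and Group B. The sponsor must say which sites apply; this review takes no position on that.
- Section 2.3 dates enrolment from December 31, 2020 to December 30, 2022, and the documents do not show whether it had begun when a correction could be made. If it has, document from treatment records what Group A patients actually received, including any difference between practitioners or over time.
- Make the title, objective and conclusion match what is delivered. If the points prove common to both arms, do not describe the result as evidence on auricular acupuncture.
- As a secondary clarification, state in item 2e whether the Group A entry refers to the practitioner only, and align it with the self-pressing instruction.

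The cost is a protocol clarification and a short instruction to practitioners, with a review of treatment records if enrolment has begun. No extra patients or visits are needed.
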